#### Secondary outcomes

Secondary outcome variables encompass behaviour-related variables related to lower back, such as LBP intensity, back health, back posture and mobility, sedentary behaviour and pain medication.

##### Behaviour-related health outcomes

To assess LBP intensity and pain-related disability*,* we use the Chronic Pain Grade Questionnaire (CPGQ),^34 35^ with instructions adapted to focus on LBP. Chronicity of LBP is assessed using a binary (yes/no) item including the criterion of constant or almost daily LBP in the previous 12 weeks.^2^

As an indicator of back health, we adapted a single item from the SF-36,^36^ which assesses subjective health: ‘How would you rate the health of your lower back?’, with a 5-point Likert scale of 1 (poor), 2 (not so good), 3 (good), 4 (very good), and 5 (excellent).

General health-related quality of life is assessed using the German SF-12 Health Survey (SF-12).^36^ Perceived stress is measured with the validated German version of the 10-item Perceived Stress Scale (PSS-10).^37 38^

##### Behavioural outcomes

To measure back posture and mobility, we use an adapted version of the Back Posture, Movement and Mobility (B-PMM) self-report questionnaire.^16^ The B-PMM self-report questionnaire consists of 13 items that assess perceived *back posture* (eg, ‘When I work, I pay attention to a posture that is gentle on my back.’), perceived back movement (eg, ‘When I am active during my leisure time, my back is also in a lot of movement (eg, twisting, bending, lifting).’) and back mobility (‘I am very flexible in the back.’). Participants can respond to the items using a 6-point Likert scale, ranging from 1 (not true at all) to 6 (extremely true). For posture and movement, the mean score is calculated from the relevant items. The validity of the B-PMM will be tested by determining the agreement with the Postural Awareness Scale (PAS),^39^ an established scale to assess the awareness of body posture in patients with chronic pain and used in the PRIA study, and with objective back measurement data from other subprojects of the research consortium.

We measure sedentary behaviour at work and during leisure time in the past 7 days by self-report using three items adapted from the IPAQ long.^31 32^ Finally, to assess pain medication, we use the Medication Quantification Scale (MQS).^40^ We record drug name, dosage (in milligrams), form (ie, pill, patch, balm, suppository, other), intake as needed or regular, intake time of day (ie, in the morning, at noon, in the afternoon, in the evening), pain localisation (ie, LBP, neck pain, headache, other), side effects (ie, nausea, vomiting, dry mouth, dizziness, sweating, tiredness, disorientation, concentration problems, stomach upset, other), and further comments, separately for each drug. The drug names will be categorised into medication subclasses, for which risk weights are available.^41^ This information can be used to calculate daily oral morphine equivalents.^42^ The relative dosage scores will be individually calculated by comparing the participant’s daily dosage with the physicians’ desk reference (current year) recommendations (eg,^43^). Thereby, three aspects of medications (drug class, dosage, risk) can be quantified.

### Determinants of behavioural and behaviour-related health outcomes

We measure (a) cognitions specific to LTPA, (b) cognitions specific to pain perception regarding the self and the social environment and (c) general cognitions and affect.

#### Activity-related cognitions

Based on the HAPA,^19^ we assess risk perception with an adapted 4-item scale introduced by Lippke *et al*,^44^ outcome expectancies with an adapted 8-item scale based on the measurement by Meng *et al*,^45^ intention to be physically active, physical activity-related self-efficacy and action planning based on the measures implemented by Sniehotta *et al*^46^ and Knoll *et al*^47^ with several adaptations (eg, for intention, the time reference is to the next 7 days instead of the last 7 days). Habit strength is measured by the Self-Report Behavioural Automaticity Index.^48^

#### Back-related and pain-related cognitions

Based on the fear-avoidance model,^49 50^ we assess pain-related cognitions, pain catastrophising using the validated German version of the Pain Catastrophising Scale,^51^ pain self-efficacy using the validated German version of the Pain Self-Efficacy Questionnaire (PSEQ),^52^ the FESS (Fragebogen zur Erfassung der schmerzspezfischen Selbstwirksameit),^53^ and fear-avoidance and endurance-related responses to pain using the Avoidance-Endurance Fast Screen.^54^

#### Behaviour-unspecific, general cognitions and affect

General self-control is measured using the validated German version of the Self-Control Scale.^55^,^57^ We also measure perceived general social support using the short form of the Social Support Questionnaire.^58^ We assess positive affect and negative affect using 12 items from the short form of the Positive and Negative Affect Schedule (short form PANAS^59^, based on PANAS^60^) in a German translation by Krohne *et al*^61^ (translation of one item adapted).

#### Social factors

We assess responses of significant others to pain reported by participants using the validated German version of the West Haven-Yale Multidimensional Pain Inventory (WHYMPI/MPI), Part II^62^ (Patienten MPI-D^63^). Part II of the WHYMPI/MPI questionnaire consists of three subscales that capture solicitous, distracting and punishing responses of a significant other (eg, spouse) while participants display pain behaviours.

### Micro-longitudinal measures

The variables collected during the EMA study phase correspond to the variables in the macro-longitudinal study. The sampling schedule and the wording of the items used in the EMA study can be found in online supplemental table 1.

#### Physical activity

Physical activity is assessed both objectively using accelerometer data and through self-report. Objective data are collected passively during waking hours using the Move 4 activity sensor.^64^ The sensor, worn on the right hip, continuously records data using a 3D accelerometer, gyroscope, barometric pressure and temperature. The device has no display and does not provide real-time feedback on activity. Combined with movisens’ DataAnalyzer analysis software, the collected data are used to calculate activity class, body position, steps, energy expenditure and metabolic equivalent of task. As part of the data cleaning process, the recording time is adjusted using the movisens’ UnisensViewer software to represent exactly 14 study days. The daily wear time is determined by subtracting the non-wear time from the total recording time. According to the guidelines of Troiano *et al*,^65^ days with 10 hours or more of wear time are considered valid.

Additionally, on each of five measurement occasions per day, participants are asked to indicate (a) whether they were physically active in their leisure time (ie, non-work-related) for at least 10 consecutive minutes, (b) the type of activity and (c) the exact times of the activity for up to two activity types per measurement occasion.

#### Low back pain

At each measurement occasion, we assess the occurrence of LBP with the binary item: ‘Since the last questionnaire, have you had or are you currently experiencing low back pain?’ (yes/no). If pain has occurred, participants report the intensity of their LBP using a single item adapted from the CPGQ^34 35^: ‘How would you rate your low back pain since the last questionnaire?’, on an 11-point scale ranging from 0 (no pain) to 10 (pain as bad as it could be). Each evening (ie, at 21:00), participants also rate the most intense LBP of the day from 0 (no pain) to 10 (pain as bad as it could be).

#### Low back health

At each measurement, we ask participants to rate their back health using a single item adapted from the SF-36^36^: ‘How has your lower back felt since the last questionnaire?’, using a 5-point Likert scale of 1 (poor), 2 (not so good), 3 (good), 4 (very good) and 5 (excellent).

#### Physical activity-related cognitions

We assess physical activity-related self-efficacy by asking: ‘At the moment, how confident are you that you can manage to be physically active in your leisure time, even if you find it difficult?’, and physical activity-related intention strength with the item: ‘At the moment, to what extent do you intend to be physically active in your leisure time?’. Both items are rated on a 10-point scale with anchors at 1 (not at all) and 9 (very much) and are based on research by Inauen *et al*.^23^ For each reported physical activity, participants also indicated whether their activity was planned or spontaneous using two items: ‘I planned this activity in advance’ and ‘I was spontaneously physically active’, and the 6-point Likert scale from 1 (I completely disagree) to 6 (I completely agree).

#### Pain-related cognitions

If participants report the occurrence of pain since the last questionnaire, we assess kinesiophobia as a potential pain-related risk factor for physical inactivity. To do this, we use a single item adapted from the Tampa Scale for Kinesiophobia^66^: ‘At the moment, I’m afraid that I might injure myself if I exercise’, rated on a scale from 1 (I completely disagree) to 6 (I completely agree). On the resource side, we assess pain self-efficacy with a single item adapted from the PSEQ^52^ (FESS^53^): ‘At the moment, I can still do things that I enjoy doing, such as hobbies or leisure activity, despite pain’, scored on the same response scale as above.

#### Pain medication

Based on the MQS,^40^ participants are asked at each measurement occasion whether they had taken any medication since the last questionnaire (yes/no). If yes, participants are asked to provide the drug name, dosage (in milligrams), form (ie, pill, patch, balm, suppository, other) and pain localisation (ie, low back pain, upper back pain, neck pain, headache, other), separately for up to four medications per measurement. In the evening (ie, at 21:00), participants report whether any side effects occurred that day.

#### Social factors

If pain has occurred, participants are asked if they have received support from other people related to their LBP since the last questionnaire (yes/no). If participants report having received support, they are asked who the support provider was (partner, family member, friend, professional caregiver, other). Furthermore, we assess received instrumental support as joint problem solving such as discussing the problem with one’s partner and taking concrete actions^67 68^ with the item: ‘The person discussed possible solutions with me or did something about the problem’, and received emotional support with the item ‘The person comforted me or hugged me’,^69^ both on a scale from 1 (I completely disagree) to 6 (I completely agree).

#### Affect, perceived stress and self-control

At the beginning of each measurement, we assess positive and negative affect by asking ‘How … do you feel at the moment?’, presenting five single positive affect items (inspired, alert, excited, enthusiastic, determined) and six negative affect items (afraid, upset, nervous, distressed, jittery, annoyed). The affect items are rated on a scale of 1 (very slightly or not at all), 2 (a little), 3 (moderately), 4 (quite a bit) and 5 (very much). The items are derived from the short form of the PANAS^59 61^ (translation of one item adapted). Using the same item format and response scale, we additionally ask participants to rate their perceived stress. Next, we measure self-control using one positively and one negatively framed item adapted from the State Self-Control Capacity Scale (SMS-5)^70^: ‘At the moment, I feel like I have no willpower left’ and ‘At the moment, I feel balanced’. Both items are rated on a scale from 1 (fully disagree) to 7 (fully agree).

#### Generalisability

At 21:00, participants report whether they worked that day and, if so, the exact hours they worked. Participants then report how typical their day was using the item ‘Now think about your usual activities on a typical weekday or weekend day like today. Was today typical for your everyday life?’, with a 5-point Likert scale of 1 (not at all or very little), 2 (a little), 3 (to some extent), 4 (a lot) and 5 (extremely). If the answer is ‘to some extent’ or lower, participants are asked to provide additional information on that day. First, with the multiple-choice item ‘What made today less typical than usual?’, with the response format 1 (less low back pain than usual), 2 (more low back pain than usual), 3 (less physical activity than usual), 4 (more physical activity than usual), 5 (other peculiarities). Second, with the open-ended question ‘What was different from usual?’.

### Power analysis

To test the micro-longitudinal hypotheses, an a priori power calculation for the LTPA outcome indicated that over n=2000 individuals (ie, number of individuals required) and at least n=14 (ie, number of repeated measures) would be required to detect small-sized population effects (given the unknown size of the cross-level interaction which is typically smaller than a main effect,^71^) with a power of ≥0.95. We aim to achieve this, but more realistically, assuming a power of ≥0.80, a sample size of at least n=200 (accounting for 30% attrition) is required to detect small-sized population effects.^72^

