**Methods and analysis:**

This prospective longitudinal study combines online questionnaires with ecological momentary assessment of health behaviours, cognitions, affect, social support and pain using a smartphone-based app (movisensXS) and continuous measurement of physical activity by accelerometry (movisens Move 4). Parameters will be recorded at baseline (T0), daily for the following 14 days (five times per day at 09:00, 12:00, 15:00, 18:00 and 21:00, resulting in up to 70 measurement occasions), 3 and 6 months later (T1 and T2). A total of 230 participants (115 individuals with cLBP and 115 without cLBP) aged 18–64 years will be enrolled. The associations between cLBP and the measured parameters will be examined using multilevel models.

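### The Power analysis attaches one effect label to two sample sizes, over 2000 and 200, that cannot share one effect, so the test to which power ≥0.80 applies is unclear

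*Protocol article*

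**What the plan says.** The Power analysis section of the protocol article gives two requirements for the micro-longitudinal hypotheses on leisure-time physical activity (LTPA).

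- For the first, it says that "over n=2000 individuals (ie, number of individuals required) and at least n=14 (ie, number of repeated measures) would be required" to detect small effects "with a power of ≥0.95". A parenthesis gives the reason: "given the unknown size of the cross-level interaction which is typically smaller than a main effect".
- It then declares this an aim of the study and moves to what it regards as realistic: "assuming a power of ≥0.80, a sample size of at least n=200 (accounting for 30% attrition) is required to detect small-sized population effects". The effect is again described as small.

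Apart from the attrition note, the only stated change between the two sentences is the power. The section gives no alpha and no numeric effect size.

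The Abstract sets enrolment: "A total of 230 participants (115 individuals with cLBP and 115 without cLBP) aged 18–64 years will be enrolled". It also gives up to 70 measurement occasions per person. Under Data analyses, Within-person hypotheses, the multilevel models use cLBP status as a person-level moderator of the within-person associations. That is a cross-level interaction.

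**The concern.** A tenfold drop in sample size is far more than a change from 95% to 80% power can buy for one effect. Either one figure is wrong, or the two belong to different effects under a common label. In both cases a reader cannot tell which planned test has power ≥0.80.

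The moderation by cLBP status is where this matters. It compares the two groups that the 115/115 enrolment creates, and the cross-level interaction is the effect mentioned beside the 2000. If the ≥0.80 is taken to cover it, a null interaction could be given more weight than the design supports.

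**Working it through.** **Inputs from the article.** Over 2000 individuals and at least 14 repeated measures at power 0.95; 200 at power 0.80 with 30% attrition; 230 enrolled; up to 70 occasions. **Assumed:** two-sided 5% alpha (z = 1.960), with other values tried below. The normal quantiles for power 0.95 and 0.80 are 1.645 and 0.842.

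**Reproducing the stated figures.** Neither 2000 nor 200 can be rebuilt, because the effect sizes and variance components are not given. An article may leave these to a fuller document. The two figures can still be tested against each other: for a fixed effect and design, N is proportional to (z_alpha + z_power)², and effect size, intraclass correlation and slope variance cancel in the ratio.

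**1. Ratio of sample sizes.**
- Expected: ((1.960 + 1.645)/(1.960 + 0.842))² = 1.656.
- Stated: 2000/200 = 10, or 2000/140 = 14.3 if 200 is enrolled and 200 × 0.7 = 140 are analysed.
- Other alphas: 1.53 at two-sided 0.01, 1.75 at one-sided 0.05, 1.90 at one-sided 0.10. Even at one-sided 0.50 it is only (1.645/0.842)² = 3.82.

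**2. What each figure implies for the other.**
- 2000 at 95% implies 2000/1.656 ≈ 1,208 at 80%.
- 200 at 80% implies 200 × 1.656 ≈ 331 at 95%; 140 analysed at 80% implies 140 × 1.656 ≈ 232.
- For both to hold, the effect behind 200 must be (2.802/√200)/(3.605/√2000) ≈ 2.5 times the effect behind 2000, or 2.9 times with 140 analysed.

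**3. Could a change in the number of occasions explain it?** Suppose 2000 assumes 14 occasions and 200 assumes all 70. With no random-slope variance, information per person rises at most fivefold (70/14). The 80% requirement is then 1,208/5 ≈ 242 analysed, still above 200.

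**4. Power for the effect behind the 2000.** Power at n analysed is Φ(3.605 × √(k·n/2000) − 1.960), with k = 1 at 14 occasions and k = 5 in the most favourable case (all 70 completed, no slope variance).

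| n | 14 occasions | 70 occasions, no slope variance |
|---|---|---|
| 140 (200 less 30%) | 0.16 | 0.57 |
| 161 (230 less 30%) | 0.17 | 0.63 |
| 200 | 0.21 | 0.72 |
| 230 | 0.23 | 0.78 |

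As the article says over 2000, these are slightly high. If 2000 is itself an enrolled number (1,400 analysed), 161/1,400 = 230/2000, so 161 analysed has the power shown for 230.

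**5. Power for the effect behind the 200.** With 161 analysed, power is Φ(2.802 × √(161/140) − 1.960) ≈ 0.85 if 140 analysed give 80%, and Φ(2.802 × √(161/200) − 1.960) ≈ 0.71 if 200 analysed are needed.

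**6. Attrition.** If 200 is enrolled, 140 must be analysed and 161 meets that. If 200 must be analysed, 200/0.7 ≈ 286 must be enrolled and 230 falls short.

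**The case against.** The strongest reply is that the two figures were never meant for one effect. The parenthesis about the cross-level interaction stands only in the 2000 sentence, the 200 sentence rests on a different citation, and small is a category rather than a number. This reading is plausible, and it would turn an arithmetical contradiction into a labelling fault. The article does not state it, however, and under it the ≥0.80 still does not extend to the planned moderation by cLBP status.

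Three stronger inferences are tempting and are not supported.

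- **That 230 is too few, or that the ≥0.80 is the wrong figure.** The clash shows that the two numbers do not share an effect, not which one is in error. Taken at face value, the 200 gives about 0.85 at 161 analysed on its more natural reading (step 5).
- **That power for the interaction is simply 16–23%.** This holds only at 14 occasions. Self-reported LTPA is asked at five prompts a day, so momentary analyses have up to 70. Daily analyses have 14. The position between the two columns in step 4 depends on a slope variance that the article does not give.
- **That the attrition allowance leaves enrolment short.** The wording most naturally means that 200 already includes attrition. As a minimum, it is met by 230.

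It can also be said that the section itself warns that the interaction's size is unknown, that the directional within-person hypotheses in the Introduction concern main associations only, and that the moderation test is nowhere called confirmatory. These points stand and limit the harm. They do not tell the reader what the ≥0.80 refers to.

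**Conclusion.** The point holds as a fault in the power statement, not as proof that the study is too small. Over 2000 at 95% and 200 at 80% cannot describe the same effect: the ratio should be about 1.66 and is at least 10, and no usable alpha raises the expected ratio above 4. Effect size and variance assumptions play no part in that comparison.

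The consequence for the moderation by cLBP status is conditional. If the 2000 belongs to the cross-level interaction, its power is well short of 0.80 at 14 occasions. Even in the most favourable case it reaches only 0.78, and that needs all 230 retained, every prompt answered and no slope variance, at two-sided 5% alpha. A one-sided 5% alpha on top of those conditions would bring it to about 0.80.

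Separately, an aim of over 2000 individuals is incompatible with enrolling 230 on any reading.

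**What to change.** Restate the Power analysis section:

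1. Name the effect to which ≥0.80 at 200 applies, and limit the claim to it.
2. Give separately the power, or the minimum detectable effect, for the cLBP-by-predictor interaction at 230 enrolled and 161 analysed, with the number of occasions assumed.
3. Delete the clause that declares the 2000 requirement an aim.
4. Say whether 200 is enrolled or analysed, noting that 230 less 30% leaves 161, which meets 140 but not 200.
5. If the restated interaction power is low, say that a null interaction will not be interpreted as evidence that the groups do not differ.

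The cost is text only, with no extra participants. The power stated for the moderation tests becomes less favourable.

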### Data analyses

Statistical analyses will be carried out both throughout the data collection process for monitoring purposes and at the end of the data collection. Descriptive statistics will be calculated for all variables (see table 1, online supplemental table 1), together with plausibility checks, assessment of distribution characteristics, identification of outliers and analysis of missing data.

#### Between-person hypotheses

The relationship between physical activity and behaviour-related health outcomes will be evaluated through regression models. Additionally, path analyses will be employed to test our hypotheses regarding longitudinal direct and indirect associations between theory-based psychological variables and LTPA (figure 1).

#### Within-person hypotheses

Intraclass correlation coefficients, Pearson correlations, as well as repeated measures correlations,^73^ will be calculated. To account for the nested structure of the micro-longitudinal data, multilevel models will be calculated with the primary outcome (ie, LTPA) and the secondary outcomes (eg, LBP intensity, back health) as dependent variables. Based on the BHBM (figure 1), psychosocial variables will be included as level-1 predictors. LBP chronicity status (ie, participants with and without cLBP) will be considered a person-level predictor, moderating associations between within-person predictors and outcomes. We will specify multilevel models with fixed and random effects. Hypothesis testing for the fixed effects will provide insights into the relationships between LBP intensity, back health, LTPA and its within-person and between-person predictors. To test the theoretical assumptions (figure 1), we will specify within-person mediation models and estimate indirect effects. In collaboration with the research consortium, we will also investigate whether the association between LTPA and its predictors is of different size depending on, for example, sex, spinal morphology and mechanics.

